## Abstract

**Background:**

Ultrasonography (US) is recommended as a standard surveillance tool for patients with a high risk of developing hepatocellular carcinoma (HCC). However, the low sensitivity of US for small HCC can lead to surveillance failure, resulting in advanced stage tumor presentations. For the early detection of HCC in high-risk patients and to improve survival and prognosis, a new efficient imaging tool with a high sensitivity for HCC detection is needed. The purpose of this study is to evaluate and compare the feasibility and efficacy of non-contrast magnetic resonance imaging (MRI) with US as a surveillance tool for HCC in patients with liver cirrhosis.

**Methods:**

MAGNUS-HCC is a prospective, multicenter clinical trial with a crossover design for a single arm of patients. This study was approved by six Institutional Review Boards, and informed consent was obtained from all participants. All patients will undergo liver US every 6 months and non-contrast liver MRI every 12 months during a follow-up period of 3 years. If a focal liver lesion suspected of harboring HCC is detected, dynamic liver computed tomography (CT) will be performed to confirm the diagnosis. After the last surveillance round, patients without suspicion of HCC or who are not diagnosed with HCC will be evaluated with a dynamic liver CT to exclude false-negative findings. The primary endpoint is to compare the rate of detection of HCC by US examinations performed at 6-month intervals with that of yearly non-contrast liver MRI studies during a 3-year follow-up. The secondary endpoint is the survival of the patients who developed HCC within the 3-year follow-up period.

**Discussion:**

MAGNUS-HCC is the first study to compare the feasibility of non-contrast MRI with US as a surveillance tool for the detection of HCC in high-risk patients. We anticipate that the evidence presented in this study will establish the efficacy of non-contrast MRI as a surveillance tool for HCC in high-risk patients.

**Trial registration:**

The date of trial registration (NCT02551250) in this study was September 15, 2015, and follow-up is still ongoing.

## Background

Hepatocellular carcinoma (HCC) is the fifth most common cancer worldwide and the second leading cause of cancer-related death [1]. Cirrhosis is the most significant risk factor for the development of HCC [2, 3]. The prognosis of HCC depends on the disease status at the time of diagnosis [4, 5]. Therefore, detection of HCC at an early stage is important, and the need for regular surveillance of high-risk patients is essential. Several studies have demonstrated that HCC surveillance leads to early detection, improved overall survival, and cost-effectiveness [2, 6–8].

The current guidelines for HCC surveillance recommend ultrasonography (US) as a screening imaging test [2, 9–11]. US is highly cost-effective, non-invasive, and radiation free [12]. However, in certain patient and under certain operator conditions, US exhibits a low sensitivity for tumor detection [13, 14]. Thus, US surveillance failure and/or suboptimal surveillance are the most common reasons for advanced stage tumor presentation. A better surveillance tool with an improved sensitivity and specificity is clearly needed.

Computed tomography (CT) and magnetic resonance imaging (MRI) exhibit increased sensitivity for detecting tumors compared with US [15, 16]. Though CT is excellent for detecting and diagnosing tumors, radiation exposure and the need for contrast agents limits its usefulness [17]. Contrast-enhanced MRI is the best imaging modality for tumor detection and differential diagnosis [15, 16, 18–22]. MRI has superior tissue contrast and poses no radiation hazard [21, 23, 24]. Recently, some studies have confirmed the efficacy of MRI as a surveillance modality for HCC [18, 25]. However, MRI examinations with contrast have disadvantages, such as limited accessibility, high cost, and the risk of contrast-related side effects. Nevertheless, the installation of MRI scanners has been increasing worldwide, increasing its accessibility [24]. In addition, non-contrast MRI also exhibits high sensitivity for detecting focal liver lesions [26] and is comparable to gadoxetic acid-enhanced MRI for detecting primary liver cancer [27]. If the MRI examination is performed with sufficient sequences to preserve superior tissue contrast without the use of contrast agents, the risk of contrast-related adverse events is eliminated, and both the cost and examination time can be reduced. With this in mind, non-contrast MRI is potentially a good alternative surveillance tool for HCC. To our knowledge, this is the first prospective study to evaluate the use of non-contrast MRI as an HCC surveillance tool in patients with liver cirrhosis.

The purpose of this study is to investigate the feasibility and efficacy of non-contrast MRI compared with US as a surveillance tool for the development of HCC in patients with high-risk factors. Specifically, we assessed the detection rate of HCC associated with biannual ultrasonography compared with annual non-contrast magnetic resonance imaging in patients with liver cirrhosis during a 3-year follow-up period.

## Methods/design

### Study design

This study is a prospective, multi-center clinical trial using a crossover design for a single arm of patients. Patients were recruited from second or tertiary hospitals in the Republic of Korea. Participants were ≥ 40 years of age with a diagnosis of liver cirrhosis who visited the hospital for HCC surveillance. US is performed every 6 months, and a non-contrast liver MRI is performed every 12 months without randomization. A flow chart of the study design is presented in Fig. 1.

**Fig. 1 Fig1:**
[figure not shown]
Flow chart providing an overview of the study design. US, ultrasonography; MRI, magnetic resonance imaging; AFP, α fetoprotein; PIVKA-II, protein induced by vitamin K absence/antagonist II; CT, computed tomography

### Ethical considerations

The study protocol was reviewed and approved by the Institutional Review Board of six participating institutions. Written informed consent was obtained from all participants by investigators. This trial was registered in an international trial registry (ClinicalTrials.gov: NCT02551250) and a domestic trial registry of the Republic of Korea (cris.nih.go.kr: KCT0001739).

### Patient recruitment and selection

Patient recruitment was performed at six participating hospitals, including the Catholic University of Korea Seoul St. Mary’s Hospital, St. Vincent’s Hospital, Uijeongbu St. Mary’s Hospital, Seoul National University Hospital, Samsung Medical Center, and Korea University Guro Hospital. Patients with a diagnosis of liver cirrhosis who visited the medical center for HCC surveillance and had no previous diagnosis of HCC were included in this study.

#### Inclusion criteria

Patient age at enrollment ≥40 yearsLiver cirrhosis diagnosed by at least one histologic or non-histologic method:Liver cirrhosis determined by liver biopsyNon-histologic diagnosis of liver cirrhosis and portal hypertensionTypical imaging features of liver cirrhosis on radiologic examinationPortal hypertension: identification of splenomegaly on radiologic examinations or identification of esophageal or gastric varices on endoscopic examination

Risk index of HCC ≥ 2.33Risk index = 1.41 (if the age is 50 years or older) + 1.65 (if the prothrombin activity is ≤75%) + 0.92 (if the platelet count is ≤100 × 10^3^/mm^3^) + 0.74 (if HCV-Ab or HBsAg test is positive) [28]

#### Exclusion criteria

Patients who declined to participate in this study and did not sign informed consentPatients with a previous diagnosis of liver cancer or other intrahepatic malignancyPatients with a history of malignancy within the previous 5 yearsPatients who are pregnant or breast-feeding

#### Sample size calculation

To calculate the number of subjects required to achieve statistical significance, the following assumptions were made:A crossover design study was planned for the two groups between US and non-contrast liver MRI.The incidence of cumulative hepatocellular carcinoma was assumed to be 15% for 3 years (5% per year) [28].The sensitivity of non-contrast liver MRI was assumed to be 80%, and the sensitivity of US was assumed to be 60% [27, 29].Type I error (α) = 5% and the power (1-β) = 80% were assumed.

A sample size of 192 patients was calculated to achieve 80% power for a difference in HCC detection of 60% for US and 80% for non-contrast liver MRI. The required sample size was 211 patients, assuming a drop-out rate of approximately 10%.

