### Surveillance

#### Surveillance period and screening interval

After the patients are enrolled, US for HCC screening will be performed at 6-month intervals (6 times), and non-contrast liver MRI will be obtained at the 6th, 18th, and 30th months (3 times) during the 3-year follow-up period. At the 6-, 18-, and 30-month visit, US and non-contrast liver MRI will be performed on the same day. The US is to be performed earlier by an abdominal radiologist and immediately followed by a non-contrast MRI. The laboratory investigations will include α-fetoprotein (AFP) and protein induced by vitamin K absence/antagonist II (PIVKA-II) within one month of the image study date. Vital signs obtained in the outpatient clinic will be monitored by reviewing the electronic medical record. Each patient will be followed-up for approximately 36 months. Based on the last screening round of the last enrolled patient, the total duration of this trial will be approximately 4 years. The schedule of follow-up examinations is presented in Fig. 2.

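### The sample size counts 36 months of HCC towards MRI detection although the last MRI is at month 30; on the inferred basis for 192, power is about 73% rather than 80% unless undiagnosed HCC at entry fills the gap

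*Protocol article*

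**What the plan says.** **Sample size calculation (protocol article).** The event count rests on this input: "The incidence of cumulative hepatocellular carcinoma was assumed to be 15% for 3 years (5% per year"). The section assumes a sensitivity of 80% for MRI and 60% for US. On error rates it says "Type I error (α) = 5% and the power (1-β) = 80% were assumed", without stating whether the test is one- or two-sided. It concludes: "A sample size of 192 patients was calculated to achieve 80% power". Drop-out of about 10% raises this to 211.

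**Surveillance period and screening interval.** For MRI: "non-contrast liver MRI will be obtained at the 6th, 18th, and 30th months (3 times) during the 3-year follow-up period". For US: "US for HCC screening will be performed at 6-month intervals (6 times"). US and MRI fall on the same day at months 6, 18 and 30. Each patient is followed for about 36 months. The text does not give the month of the first or last US, and the timeline figure is not available in the copy reviewed.

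**Endpoints and Statistical analysis.** The primary endpoint compares detection by 6-monthly US with detection by yearly MRI over the 3-year follow-up, using the McNemar test.

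**Diagnostic work-up for HCC confirmation.** Patients not diagnosed with HCC have a dynamic CT after the last round, to look for false negatives.

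**The concern.** The incidence input covers 36 months and the MRI schedule covers 30. Nothing in the article lowers either the 15% incidence or the 80% MRI detection for the last six months. An HCC that first becomes detectable after month 30 cannot be found by the trial's MRI, so it cannot supply the MRI-only pair that drives the McNemar test. It can still be found by a later US or by the closing CT, and would then count as an MRI miss.

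The trial expects fewer than 30 events, so losing about five matters. If the result is null, readers will judge it against a claimed 80% power that the schedule may not provide. If the handling of late HCCs is left open, it could be chosen after the data are seen.

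**Working it through.** **Inputs from the protocol article:** incidence 5% per year (15% over 3 years), sensitivities 80% and 60%, alpha 5%, power 80%, N = 192, MRI at months 6, 18 and 30, McNemar test.

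**Inputs not stated there, so assumed:** sidedness, the split of discordant pairs, a constant onset rate, and the number of undiagnosed HCCs at entry.

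**1. Reproducing 192.** Let p10 be the share of HCCs found by MRI only, p01 the share found by US only, d = p10 − p01 and s = p10 + p01. The normal approximation for McNemar is

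n = [z_α·√s + z_β·√(s − d²)]² / d².

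Take p10 = 0.20 and p01 = 0 (every HCC found by US is also found by MRI), with a one-sided 5% test:

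n = [1.645·√0.20 + 0.842·√0.16]² / 0.04 = 28.74 HCCs, and 28.74 / 0.15 = 191.6, so 192.

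Other bases tried do not give 192:
- the same split, two-sided: 246
- independent detections (p10 = 0.32, p01 = 0.12): 440 one-sided, 560 two-sided
- McNemar on all patients with 12% v 9% detected and no US-only detections: 204 one-sided, 260 two-sided
- unpaired comparison of two proportions: roughly 427 to 607

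The one matching basis divides by the full 15%, so it credits MRI with HCCs from all 36 months.

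**2. HCCs within reach of the MRI schedule.**
- 36 months: 192 × 0.15 = 28.8
- 30 months: 192 × 0.05 × 2.5 = 192 × 0.125 = 24.0
- Difference: 4.8, one sixth of the total (15.6% under a constant hazard that reaches 15% at 3 years)

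**3. Power at 192.** Power = Φ{[d·√n − z_α·√s] / √(s − d²)}.

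| Handling of HCCs arising after month 30 | n | p10 | p01 | One-sided | Two-sided |
|---|---|---|---|---|---|
| As planned, all within reach of MRI | 28.8 | 0.200 | 0 | 80.1% | 68.9% |
| Left out | 24.0 | 0.200 | 0 | 72.9% | 60.2% |
| Kept, found by neither test | 28.8 | 0.167 | 0 | 72.5% | 60.0% |
| Kept, month-36 US finds 60% | 28.8 | 0.167 | 0.100 | 16.9% | 10.1% |

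In the last two rows p10 = (5/6) × 0.20. In the last row p01 = (1/6) × 0.60, and overall detection is (5/6) × 80% = 66.7% for MRI against 60% for US.

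With independent detections and a two-sided test, going from 28.8 to 24.0 HCCs lowers power from 36.0% to 30.6%.

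**4. Drop-out margin.** If all 211 patients completed, 211 × 0.125 = 26.4 HCCs, and one-sided power is 76.7%.

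**5. Undiagnosed HCC at entry.** Suppose such tumours carry the same 80% v 60% contrast and the late HCCs are left out. Then n = 192 × (0.125 + prevalence):

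| Prevalence at entry | HCCs | One-sided power |
|---|---|---|
| 0% | 24.0 | 72.9% |
| 1.0% | 25.9 | 76.0% |
| 1.7% | 27.2 | 77.9% |
| 2.5% | 28.8 | 80.1% |
| 4.2% | 32.0 | 83.9% |

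The 1.7% and 4.2% rows assume earlier 6-monthly US at 60% sensitivity, misses independent between rounds and 5% onset per year. Just after a US the undetected share is 2.5% × (0.4 + 0.16 + …) = 1.7%. Just before the next it is 1.7% + 2.5% = 4.2%.

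At 2.5% prevalence with the late HCCs kept in (28.8 + 4.8 = 33.6 HCCs), power is 79.7% if neither test finds them. It is only 25.0% if a month-36 US finds 60% of them.

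**The case against.** The strongest objection concerns tumours present at entry. The sample size section gives an incidence and says nothing about entry prevalence. The recruitment and exclusion criteria bar only a previous diagnosis, no CT or MRI to clear the liver at entry is described, and patients were recruited because they attended for surveillance. Some undiagnosed HCC at entry is plausible, and about 2.5% of patients would restore the planned count. This stands: the size of the shortfall depends on a quantity that the protocol leaves open, and it could be zero.

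A second objection is that the 5% per year may count diagnoses rather than onsets. Some HCCs diagnosed in months 30 to 36 could then have been visible on the month-30 MRI. This also stands, and the article does not settle it. In the other direction, a patient diagnosed after a US-only round leaves the trial and cannot become a later MRI detection, so one sixth may also be too small.

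A third is that the 80% may mean detection over the whole 3-year programme, late misses included. MRI would then have to find 0.80 / (5/6) = 96% of the HCCs arising by month 30. The article does not say that this is meant, and it presents the 80% as the sensitivity of the test.

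Finally, the window is not the main threat to power. With all 28.8 HCCs, two-sided power is already 68.9%, or 36.0% with independent detections. That is true, but the window costs power on each of these bases as well.

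A reader might infer that one sixth of the planned HCCs can never be MRI detections, or that 192 is a miscalculation and 28.74 / 0.125 = 230 patients are required. The documents do not support either as fact. Both need zero undiagnosed HCC at entry and an onset-based incidence, and 192 does follow from the stated inputs on one inferred basis.

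**Conclusion.** The mismatch is real and stands on the page: the event count spans 36 months, the MRI schedule ends at month 30, and no allowance links them. With constant onset at 5% per year and no undiagnosed HCC at entry, about 4.8 of 28.8 HCCs fall outside the reach of MRI. On the only basis found that reproduces 192, power is then about 73% instead of 80%, whether the late HCCs are left out or kept and found by neither test. It is about 17% if US runs to month 36 and finds 60% of them. Six examinations at 6-month intervals, three of them at months 6, 18 and 30, fit that schedule, but the text does not confirm it.

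The conclusion rests on an inferred test basis (one-sided, no US-only detections) and on an unstated entry prevalence. A prevalence of about 2.5% would remove the shortfall, except in the month-36 US case.

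A reader might also infer that the primary comparison should be cut to HCCs arising by month 30. It should not. The endpoint compares the two programmes over 3 years, and dropping late HCCs that a later US might find would favour MRI and hide a cost of the annual schedule.

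**What to change.** 1. In the sample size section, restate the power for the planned number using the HCCs that the MRI schedule can detect: 30 months × 5% per year = 12.5%, or 24 per 192. State the sidedness and the discordance assumption behind the figure.
2. State the assumed prevalence of undiagnosed HCC at entry and show power over a range, for example 0% to 4.2% as tabulated in the working.
3. Keep the primary McNemar comparison on all HCCs of the 3-year follow-up, as the Endpoints section has it. Report the comparison limited to HCCs up to the month-30 round as a sensitivity analysis, specified before the data are examined.

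The cost is a few sentences, probably a less favourable power figure, and one additional analysis of data already collected. Visits, tests and enrolment do not change.

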### Endpoints

Primary endpoint: comparison of the HCC detection rate by US performed at 6-month intervals with that of yearly non-contrast liver MRI during a 3-year follow-up.

Secondary endpoint: survival of the patients who developed HCC during the 3-year follow-up period.

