MRI is the most sensitive modality for the detection of HCC [15]. However, MRI is not commonly used as a screening modality due to the high cost, long examination time, low accessibility and the risk of adverse effect from the contrast media. There is also little evidence supporting the efficacy of MRI for HCC surveillance. In this trial, we modified two factors to counter these objections to using MRI examination as a surveillance tool. First, the MRI will be performed without the use of intravenous contrast. Arterial enhancement after contrast injection is one of the major criteria for diagnosing HCC. However, in reality, intravenous contrast is not necessary in a surveillance step. Rather, it is more important to detect focal hepatic lesions with high sensitivity in high-risk patients. T2WIs have a high sensitivity for detecting focal liver lesions, and DWIs are effective in detecting and characterizing HCC in cirrhotic patients [34, 35], especially small HCC (<2 cm) [36]. In addition, high b-values on DWI offer excellent specificity in distinguishing HCC from benign cirrhotic nodules and pseudo-lesions [37]. If the MRI examination is performed using these basic sequences without contrast, this method is quite adequate for HCC surveillance. The study also takes only 10–15 min, which is less time than when contrast-enhanced dynamic images are obtained.

In the study protocol, MRIs will be obtained annually and US bi-annually. MRIs will be obtained every 12 months, an acceptable interval range for HCC surveillance based on the recommendation to obtain imaging studies every 6 to 12 months [15]. Thus, the high cost of MRI will be offset by fewer examinations. In addition, the increased time interval between studies will be offset by the superior sensitivity of MRI for HCC detection. In summary, fewer studies compensated by superior sensitivity can decrease the overall cost of MRI and increase its appeal as a screening tool.

This is the first study to evaluate the feasibility of non-contrast MRI compared with US as a surveillance tool for detecting HCC in high-risk patients. We expect that the results support the efficacy of non-contrast MRI as a screening tool for HCC in this patient population.

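### The 60% v 80% behind the stated power takes no account of six ultrasound examinations against three MRIs, or of exit at diagnosis, so the 80% power is not shown to belong to the primary endpoint

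*Protocol article*

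**What the plan says.** Under Sample size calculation, the article assumes: "The sensitivity of non-contrast liver MRI was assumed to be 80%, and the sensitivity of US was assumed to be 60"%. The incidence assumption is "The incidence of cumulative hepatocellular carcinoma was assumed to be 15% for 3 years (5% per year"). Error rates are given as "Type I error (α) = 5% and the power (1-β) = 80% were assumed", with no statement of one- or two-sided testing. The result is: "A sample size of 192 patients was calculated to achieve 80% power for a difference in HCC detection of 60% for US and 80"% for MRI. The same two percentages thus appear first as sensitivities and then as detection rates, with nothing in between. Dropout takes the number to 211.

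The primary endpoint under Endpoints is a "comparison of the HCC detection rate by US performed at 6-month intervals with that of yearly non-contrast liver MRI" over three years. Under Surveillance period and screening interval, "US for HCC screening will be performed at 6-month intervals (6 times"), while MRI is done three times, at months 6, 18 and 30. Diagnostic work-up for HCC confirmation ends participation once dynamic CT diagnoses HCC, and gives patients still undiagnosed after the last round a closing CT. Statistical analysis names the McNemar test for the difference in detection rate.

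The Discussion treats sensitivity and interval as separate quantities: "the increased time interval between studies will be offset by the superior sensitivity of MRI for HCC detection".

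**The concern.** A test's sensitivity and the share of tumours a repeated programme finds over three years are different quantities. US gets two examinations for each MRI, so its programme-level rate can exceed 60%. MRI can fall below 80%, because a tumour arising after month 30 gets no MRI and one found at a US-only visit leaves before its next MRI. The sample-size section has no step for any of this.

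At stake is the stated power. If the true programme-level difference is small or reversed, the trial does not have 80% power for its primary endpoint. A null or reversed result could then be misread as evidence about MRI's sensitivity when it reflects the schedule.

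**Working it through.** **1. The plan's own figure.** Inputs from Sample size calculation: 60%, 80%, 15% incidence, alpha 5%, power 80%. The asymptotic McNemar formula is

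n(HCC) = [z_a·√p + z_b·√(p − d²)]² / d²,

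where p is the discordant proportion and d the difference. With one-sided alpha 5% (z_a = 1.645, z_b = 0.842), MRI-only 0.20 and US-only 0, p = d = 0.20:

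(1.645·√0.20 + 0.842·√0.16)² / 0.04 = 28.74 HCC cases; 28.74/0.15 = 191.6, so 192.

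The stated number reproduces, so the question is the effect size and not the arithmetic. On this reconstruction no tumour is found by US alone. At 15% incidence, 192 patients yield 0.15 × 192 ≈ 29 cases.

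**2. Two US examinations against one MRI.** With independent misses, two US find 1 − 0.4² = 84%, against 80% for one MRI. With fully persistent misses (a tumour missed once by US is always missed by US), US stays at 60%.

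**3. Full schedule.** Assumptions not in the article: 60% and 80% apply at each examination; no tumour is present at entry; onset is uniform over 0-36 or 0-30 months; US runs at months 6-36 or 0-30 (the text does not say, and Fig. 2 was not available for this check); misses are independent or fully persistent, the same for both tests; same-day readings are independent; every detection is confirmed on CT.

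Examples for onset over 0-36 months:
- MRI, independent, no exit: (6/36)(0.992) + (12/36)(0.96) + (12/36)(0.80) + (6/36)(0) = 75.2%.
- US at 6-36, independent, no exit: the mean of 1 − 0.4^k for k = 1 to 6 = 88.9%.
- MRI, persistent, with exit: half of tumours first meet an MRI visit, a third first meet a US-only visit and reach MRI only if US misses them, and a sixth arise after the last MRI: 0.5(0.80) + (1/3)(0.4 × 0.80) + 0 = 50.7%.

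Detection rates (%) and gap, MRI minus US, in points (gaps from unrounded rates):

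| US months | Onset | Misses | No exit: US / MRI / gap | With exit: US / MRI / gap |
|---|---|---|---|---|
| 6-36 | 0-36 | independent | 88.9 / 75.2 / −13.7 | 71.9 / 51.7 / −20.2 |
| 6-36 | 0-36 | persistent | 60.0 / 66.7 / +6.7 | 60.0 / 50.7 / −9.3 |
| 0-30 | 0-36 | independent | 72.3 / 75.2 / +2.9 | 60.7 / 51.7 / −9.0 |
| 0-30 | 0-36 | persistent | 50.0 / 66.7 / +16.7 | 50.0 / 50.7 / +0.7 |
| 6-36 | 0-30 | independent | 94.7 / 90.2 / −4.5 | 74.3 / 62.0 / −12.2 |
| 6-36 | 0-30 | persistent | 60.0 / 80.0 / +20.0 | 60.0 / 60.8 / +0.8 |
| 0-30 | 0-30 | independent | 86.8 / 90.2 / +3.4 | 72.9 / 62.0 / −10.8 |
| 0-30 | 0-30 | persistent | 60.0 / 80.0 / +20.0 | 60.0 / 60.8 / +0.8 |

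**4. Wider assumptions.** Allowing 20% of tumours at entry, or maximally concordant same-day readings, widens the with-exit range to about −25 to +5. Across those with-exit scenarios, power to show MRI better with 29 cases is at most about 9% (one-sided, normal approximation) or 3% (two-sided exact). Without exit, the +6.7 case with concordant readings (MRI-only 0.167, US-only 0.100) would need about 369 HCC cases, or 2,459 patients, by the formula that gave 192.

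**5. Different miss patterns by test.** If US misses persist but MRI misses are independent, the no-exit gap can exceed 20 points: 75.2 − 50.0 = +25.2, or 90.2 − 60.0 = +30.2. With exit and onset over 0-30 months, averaging the five six-month onset windows gives MRI (0.8768 + 0.384 + 0.864 + 0.32 + 0.80)/5 = 64.9%, against 60% for US: +4.9.

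**The case against.** The strongest reply is that the section never calls 60% and 80% per-examination values. They stand beside a 3-year incidence and are restated as detection rates, which also fits programme-level figures, and the cited sources are not at hand. This stands: the per-examination reading is an inference from the unqualified wording, the unchanged reuse of both numbers, and the Discussion's separation of sensitivity from interval.

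Second, the results turn on unstated assumptions. In the first row of the table, tumours arising in months 30-36 alone contribute (1/6) × 60% = 10 of the 13.7 points. This also stands, so the figures are ranges and not predictions.

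Third, the 84% example takes the extreme least favourable to MRI. The Discussion attributes weak US performance to obesity, fatty liver and macronodular cirrhosis, which would tend to persist between visits. That is fair, and it is why persistent misses are shown throughout. Persistence restores a large MRI lead only when early exit is ignored; with the exit rule, the persistent rows run from −9.3 to +0.8.

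A reader might infer that MRI's lead can never be 20 points. That is false: +20 appears in two no-exit rows and is exceeded in step 5. A reader might also take the Discussion to concede that no large net gap is expected. It says only that sensitivity offsets the interval, gives no net size, and goes on to expect support for MRI.

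**Conclusion.** The stated 80% power is not shown to belong to the stated primary endpoint. If 60% and 80% are per-examination values, and repeat misses behave alike for both tests, the 20-point gap survives at programme level only with fully persistent misses, no early exit and no tumour arising after the last MRI. The protocol's own exit rule breaks the second condition. Under that rule the gap is about −20 to +1 points (onset 0-36 months) or −12 to +1 (onset 0-30), and −25 to +5 across the wider scenarios. These figures rest on the onset, dependence, US-timing and CT-confirmation assumptions listed above.

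If 3-year programme rates were meant, the defect is narrower: the text should say so and explain how they allow for the schedule. The document does not support the stronger inference that the trial is underpowered under every reading of its inputs.

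**What to change.** In Sample size calculation, state whether 60% and 80% are per-examination sensitivities or 3-year programme rates. If per-examination, give the expected programme-level rates for six US and three MRIs with exit at CT diagnosis, over a stated range from independent to fully persistent misses, and restate the power for the endpoint as defined. Give the months of the six US examinations and the onset assumption used.

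Add the same-day paired comparison at months 6, 18 and 30 as a supporting analysis, since that is where a 60% v 80% contrast applies most directly. Note there that tumours found and confirmed at an intervening US will already have left. Keep the programme comparison as primary, because replacing it would change the trial's question.

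The cost is a rewritten sample-size paragraph and one added analysis on data already collected. Enrolment does not change. The price is a less favourable stated effect and power.
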